# Testing a systematically braided alcohol reduction and HIV status neutral intervention among people receiving STI care in Malawi: study protocol for a pilot hybrid type 1 effectiveness-implementation randomized controlled trial

**DOI:** 10.3389/fpubh.2025.1572288

**Published:** 2025-04-30

**Keywords:** evidence based intervention, alcohol reduction, HIV status neutral, sexually transmitted infection, preexposure prophylaxis, antiretroviral therapy

## Abstract

**Background:**

Heavy alcohol use is common in Malawi among people receiving sexually transmitted infections (STI) care and is a critical barrier to the success of HIV prevention and treatment efforts.

**Methods:**

This protocol presents a pilot hybrid type 1 effectiveness-implementation trial evaluating the short-term effectiveness and implementation of a scalable evidence-based intervention (EBI) to reduce alcohol use and provide HIV prevention and treatment counseling for people with heavy drinking receiving STI care in Malawi. We developed a 3-session intervention, Treat4All, that uses motivational interviewing, problem-solving skills, psychoeducation, alcohol refusal, HIV prevention and treatment skills building, and goal setting to reduce alcohol and facilitate engagement in HIV prevention and treatment. We have also integrated HIV prevention content to focus on persistent PrEP use and HIV treatment adherence to improve antiretroviral therapy (ART) adherence and viral suppression. We will conduct a two-arm pilot randomized controlled trial (RCT) in an STI care setting in urban Malawi to compare the preliminary effectiveness and implementation of Treat4All to usual care for decreasing the proportion of heavy drinking days, corroborated with phosphatidylethanol, an alcohol biomarker, and improving HIV outcomes (viral suppression among PWH; PrEP use among those at risk). We will randomly assign 160 people receiving STI care in Lilongwe who report heavy drinking (*n* = 80 people with HIV; PWH; *n* = 80 people at high risk of HIV acquisition) to Treat4All or usual care.

**Discussion:**

Our study will produce a systematically braided, scalable HIV status-neutral EBI for alcohol reduction and optimization of HIV prevention and treatment behaviors to evaluate in a larger effectiveness-implementation trial. Our study will directly expand alcohol reduction and HIV status-neutral programs for alcohol-impacted populations throughout sub-Saharan Africa and other regions where alcohol contributes to the ongoing HIV epidemic.

**Clinical trial registration:**

ClinicalTrials.gov, NCT06668363.

## Highlights

This study advances alcohol reduction and HIV status-neutral interventions for both PWH and those at risk for HIV.It targets an underserved population—individuals with heavy alcohol use in STI care—broadening the scope of HIV prevention efforts.Incorporating alcohol biomarkers (phosphatidylethanol, PEth) offers an objective measure to enhance accuracy in evaluating intervention efficacy.The research sets the stage for future hybrid effectiveness-implementation trials focused on cost-effectiveness and long-term outcomes.It provides critical insights for scaling and systematically braiding alcohol reduction and HIV prevention programs across sub-Saharan Africa and beyond.

## Introduction

1

Forty years into the HIV epidemic, people living in sub-Saharan Africa (SSA), including Malawi, continue to experience a disproportionate burden of HIV infection. In Malawi, HIV prevalence among adults aged 15–49 is 6.7%, with new infections ongoing (10,000 persons/year; HIV incidence rate of 0.98/1,000 adults), and nearly 30% of people with HIV (PWH) remaining virally unsuppressed (1). Non-HIV sexually transmitted infections (STIs) are common among PWH and those at high risk of HIV and are a marker of condomless sex, multiple partners, high-risk sexual networks, increased vulnerability to HIV, undiagnosed and unsuppressed HIV, and increased viral shedding (among PWH) (2–6). In our prior work, HIV prevalence among people receiving STI care in Malawi was 22% (7). Among people with STI/HIV co-infection in the largest STI clinic in the capital of Malawi, 72% were either newly diagnosed with HIV or previously diagnosed and not on antiretroviral therapy (ART) (8). People with an STI are a priority target population for interventions to improve HIV prevention and treatment. Given this context, people with an STI represent a key population for interventions that improve HIV prevention and treatment.

Heavy alcohol use significantly contributes to STI risk and undermines HIV prevention and treatment efforts (9–11). Nearly 40% of adults in Malawi drink alcohol, with approximately half of those (47%) reporting hazardous drinking, defined as an Alcohol Use Disorders Identification Test (AUDIT) score of ≥3 for women and ≥4 for men (10, 12, 13). Between 40–50% of PWH globally have a history of heavy or hazardous alcohol use (14). Among PWH, hazardous alcohol use is associated with poor adherence to ART, resulting in poor HIV viral suppression, which may lead to opportunistic infection and death (15). Heavy alcohol use has been consistently associated with adverse HIV treatment outcomes, including delayed ART initiation, suboptimal ART adherence, and virologic failure (16–19). Among people at high risk for HIV, heavy drinking has been associated with reduced HIV testing, repeat STIs, and condomless sex, compromising the success of HIV prevention strategies (20–26). Heavy drinking may also be associated with suboptimal outcomes throughout the pre-exposure prophylaxis (PrEP) care continuum, including low PrEP awareness and interest and suboptimal adherence to PrEP (27, 28). These disruptions across the HIV care and prevention continuum pose a significant barrier to achieving the UNAIDS 95–95-95 targets, which rely on effective diagnosis, sustained treatment, and viral suppression (29). Effectively addressing heavy alcohol use among people with STIs has the potential to improve HIV prevention and treatment outcomes and reduce HIV acquisition and transmission. HIV status-neutral interventions that target alcohol reduction and HIV prevention and treatment among people with STIs may ultimately reduce HIV incidence by simultaneously increasing viral suppression among PWH and PrEP use among people at risk for HIV.

Despite the prevalence of heavy alcohol use and its detrimental impact on HIV outcomes, evidence-based interventions (EBIs) for alcohol reduction remain scarce across SSA, especially in HIV and sexual health care settings (30, 31). In 2020, only 30% of surveyed HIV clinics in SSA, and just 19% in Southern Africa, reported providing any alcohol screening or treatment. Integrating EBIs to reduce alcohol use into sexual health care settings could reach a large, high-risk population, improving both HIV prevention and treatment outcomes (12, 31–34). Malawi’s national commitment to scaling up alcohol use treatment and the recent implementation of PrEP services in 2021 make it a prime location for this work.

Project TrEAT, a Trial for Early Alcohol Treatment, is a brief (2-session), highly effective, scalable, evidence-based intervention (EBI) for alcohol use reduction (35–40). TrEAT has been successfully tested with diverse populations of PWH and has led to significant improvements in the percentage of days abstinent from alcohol and viral suppression (35, 38, 39). TrEAT has not been adapted for the shifting HIV care environment to include ART and PrEP use content for both PWH and people at high risk. To address this gap, we have developed a new, systematically braided intervention called Treat4All. This three-session intervention integrates HIV status-neutral counseling with TrEAT, focusing on problem-solving, skills-building for alcohol refusal and HIV prevention and treatment use, and goal-setting (41). Delivered through the use of motivational interviewing approaches, Treat4All aims to reduce heavy drinking and improve HIV outcomes, specifically viral suppression for PWH and PrEP use for those at high risk of HIV.

The objectives are to evaluate short-term effectiveness and implementation of Treat4All for reducing heavy drinking and optimizing HIV outcomes, specifically viral suppression among PWH and PrEP use among those at high risk at 6 months post-enrollment. Additionally, we will explore enablers and barriers of the Treat4All intervention response with responders and non-responders.

## Methods

2

### Trial design

2.1

We are conducting a pilot hybrid type 1 effectiveness-implementation randomized controlled trial in one STI care setting in Lilongwe to compare the efficacy of Treat4All to usual care for decreasing the proportion of heavy drinking days and optimizing HIV outcomes (viral suppression among PWH; PrEP use among those at risk). We will examine the proportion of heavy drinking days, corroborated by a random subsample using phosphatidylethanol (PEth), and successful engagement in HIV prevention and treatment at 6 months. Using mixed-methods data collection, we will also assess the acceptability, feasibility, and fidelity of the Treat4All.

### Participants and study procedures

2.2

Our primary objective is to evaluate the short-term effectiveness and implementation of Treat4All for decreasing heavy drinking and optimizing HIV outcomes (viral suppression among PWH and PrEP use among those at a high risk of HIV). We will randomly assign 160 people receiving STI care at the Bwaila STI clinic in Lilongwe, Malawi, who reported heavy drinking (*n* = 80 PWH; *n* = 80 people at high risk of HIV acquisition), to Treat4All or usual care.

Guided by the situated Information, Motivation, and Behavior (sIMB) model, we will conduct semi-structured interviews with responders and non-responders of Treat4All 6 months post-enrollment (*n* = 30). Responders will include those who have decreased the proportion of heavy drinking days or have achieved HIV outcomes. Non-responders will be those who did not.

### Eligibility criteria

2.3

In coordination with the STI Clinical Director, we will host clinic meetings to introduce the project and study plans to clinical patients. Patients receiving STI care will be provided with information about the project by clinic staff, and those interested will be screened by clinic staff for eligibility.

Patients receive routine opt-out HIV testing as part of their usual care (UC). To be eligible, patients must: (1) be aged 18 or older, (2) be receiving care at the Bwaila STI clinic, (3) report recent heavy drinking (≥4 drinks a day in the past 30 days for men and ≥3 drinks a day in the past 30 days for women), (4) be willing to receive an HIV test at study enrollment, (5) report not taking ART or having a recent history of unsuppressed viral load (>1 viral load test with >40 copies of HIV-1 RNA per milliliter in the past 2 years) [for PWH] *or* not currently taking a PrEP prescription (self-reported taking <1 pill per week) [for those at risk of HIV], (6) plan on residing in Lilongwe for the next 6 months, (7) not participating in other HIV or alcohol programs, (8) ability and willingness of participant to provide informed consent, and (9) willingness to provide contact/locator information to be contacted for follow-up study activities.

Patients will be ineligible if they are: (1) unable to participate in study activities due to psychological disturbance, cognitive impairment, or threatening behavior, (2) unwilling to provide locator information, (3) pregnant or breastfeeding (given that a greater understanding of alcohol use during pregnancy would be warranted but limited within the planned sample) (42, 43), (4) unwilling to receive an HIV test, (5) at risk of experiencing alcohol-related withdrawal symptoms (measured using an adapted Clinical Institute Withdrawal Assessment Alcohol Scale Revised [CIWA-AR]) (44), (6) have acute physical or mental illness, including suicidal thoughts or behaviors, (7) serious illness including tuberculosis or opportunistic infection, requiring systemic treatment and/ or hospitalization, (8) active drug dependence that in the opinion of the site investigator, would interfere with adherence to study requirements, or (9) any other condition that in opinion of the study investigator would compromise the safety of the study participant or study staff or would prevent proper conduct of the study. If they are determined to be eligible, the research staff will administer informed consent and schedule their visits. Patients will be made aware of the voluntary and confidential nature of the study. Trained research assistants will collect the required data.

### Intervention

2.4

The intervention arm (Treat4All) will include a total of 80 participants who will be randomly allocated to Treat4All. The intervention will follow a workbook but will also be flexible to allow for discussion of the intersection of alcohol, HIV prevention and treatment, and sexual risk to emerge naturally within the context of the sessions. There will be three sessions, and the actual session content of Treat4All will be tailored to a function of an individual’s particular issues and HIV status.

Treat4All is a systematically braided intervention in which three EBIs are systematically blended based on common elements to create an integrated alcohol reduction and HIV status-neutral intervention (45). Briefly, the braiding process included five steps: (1) Initial expert consultations; (2) formative qualitative interviews (total *n* = 40; *n* = 5 STI care providers, *n* = 5 bar/bottle shop staff and owners, and *n* = 30 receiving STI care with heavy drinking, i.e., *n* = 15 with HIV and *n* = 15 at risk for HIV); (3) identification of core mechanisms; (4) initial draft of braided components; and (5) follow-up expert consultations on the initial draft. Fleming’s Project TrEAT, a Trial for Early Alcohol Treatment, was enhanced with culturally appropriate HIV status-neutral content adapted from HIV Prevention Trial Network studies 082 and 074 for HIV prevention and treatment counseling, respectively.

Guided by the situated Information, Motivation, and Behavior (sIMB) framework, which emphasizes the role of information, motivation, and behavioral skills in sustaining health behaviors, Treat4All represents a novel approach to address alcohol use and HIV in Malawi. The sIMB uses the three core determinants of initiating and sustaining behavior over time: information, motivation, and behavioral skills (41). The information determinant refers to the facts and knowledge of the behavior (41). Motivation refers to the attitudes and beliefs about the positive and negative consequences of adopting health-promoting patterns of behavior at the personal and social levels (41). Lastly, behavioral skills refer to the abilities and self-efficacy that guide the successful adoption of behavior patterns (13, 46, 47). This framework ensures that individuals have the knowledge, motivation, and skills needed to initiate and maintain health-promoting behaviors.

In addition, Treat4All leverages the AIM (Assess, Identify, Make a Plan) activity from the Life Steps behavioral activation framework, which was previously adapted for HIV prevention in HPTN 082. Completing the role of information, motivation, and behavioral skills, AIM can help empower participants to address alcohol use and HIV prevention and treatment through structured goal-setting and action planning. In this adapted AIM model, participants will be encouraged to assess their current behaviors and health status, particularly those related to alcohol use and HIV infection. They then will identify personalized goals that align, such as fewer days of drinking or initiating PrEP. Finally, they will make a plan by setting specific, achievable steps that integrate goals into daily life, supported by motivational and practical tools. This tailored approach enables participants to engage actively in their health improvement journey, reinforcing self-efficacy and supporting long-term behavioral changes in areas critical to alcohol use and HIV.

Each 30-min session, delivered over three weeks (up to 12 weeks allowed), provides personalized feedback on alcohol use, discusses its health impacts, and addresses reasons for reducing consumption. Participants will identify risky situations, learn handling strategies, and set behavioral goals. Alcohol-related content covers drinking patterns, harm, and change strategies, while the HIV component promotes ART adherence and PrEP for those at risk. This approach, using problem-solving, skills building, and goal setting, aims to reduce heavy drinking and improve HIV care engagement, fostering ART adherence, viral suppression, and PrEP uptake. The formative qualitative interviews informed the culturally tailored content, ensuring that the intervention addressed locally relevant drinking behaviors, HIV-related challenges, and effective, context-specific strategies for change. Interventionists will use a Treat4All booklet and a collaboratively developed flipchart in each session to enhance intervention fidelity, participant engagement, and comprehension. The booklet provides structured guidance to ensure consistent delivery of core content, while the flipchart serves as a visual aid, illustrating key concepts that support participant understanding. This flipchart, created with input from both US- and Malawi-based intervention teams and a graphic designer, incorporates culturally relevant and accessible visuals tailored to the goals of the intervention. For example, intervention materials include images of common Malawian drinks to illustrate the alcohol content of standard drinks. To minimize potential bias from the Chichewa translation, all intervention materials and instruments underwent translation and back-translation processes, followed by role-playing by research staff to ensure linguistic and cultural accuracy. Any discrepancies were resolved through consensus with bilingual experts to maintain consistency and avoid confounding the findings. This collaborative approach ensures that the materials are both engaging and effective in conveying essential information.

The intervention sessions will be delivered by a trained intervention counselor with a diploma in psychology and a certificate of addiction counseling in Malawi. Intervention counselors will complete a weeklong in-person training at the UNC Project in Lilongwe. Training included a comprehensive review of the interventionist training manual, booklets, and flipcharts. The interventionist training manual was developed to serve as a resource, providing an overview of the study and Treat4All intervention, educational components on alcohol-related harm and HIV prevention and treatment, the importance of ensuring patient confidentiality, skills building, and counseling techniques (e.g., motivational interviewing, problem-solving skills, and goal setting). Additionally, it includes information on self-care for interventionists to focus on reducing stress and burnout. The training also included discussions on session content flow, making any necessary revisions, and reviewing the standard operating procedures. Interventionists engaged in role-playing and empty-chair practices to enhance their session delivery skills. Role-play and empty-chair practice continued for 3 weeks, with weekly debriefs discussing successes and challenges.

All Treat4All sessions will be audiotaped, and a random subsample of 20% will be reviewed to ensure intervention fidelity to the core intervention components. A bilingual Chichewa-English speaker who has received training in both intervention manuals listens to one or two audio-recorded intervention sessions biweekly and rates the interventionist’s fidelity to the intervention. The ratings will be discussed in weekly supervision meetings.

A total of 80 participants will be randomly allocated to the UC group. UC includes sexual risk reduction counseling that integrates messaging on reducing alcohol use before sex and the recommendation to abstain from or reduce alcohol while on ART, with limited further guidance. Participants in this arm will continue to receive all STI- or HIV-related services.

All participants, regardless of the study arm, will receive counseling from a trained HIV counselor in the STI clinic as part of the standard of care. Condoms will be available in the clinic. All PWH or newly diagnosed participants will be referred to a Lighthouse Trust HIV clinic, as needed per the standard of care.

### Effectiveness outcomes and study measures

2.5

Participants will complete enrollment and baseline data collection before being randomly allocated the assignment to one of the two study arms. Participants will receive a random assignment through the prepared envelopes to Treat4All or UC at a ratio of 1:1. Masking of participants and intervention counselors to study arm assignment in the field is not feasible because of the nature of the interventions; data collection staff, analysts, and investigators will be masked to the study assignment until analyses are complete. Participants will be followed up for 6 months (Table 1).

**Table 1 tab1:** Schedule of enrollment, interventions, and assessments.

Timepoint	Enrollment	Baseline	Allocation	Post-allocation		
	*t_0_*	*t_0_*	*t_0_*	*t_0_*	Month 3	Month 6
Enrollment						
Eligibility screen	X					
Informed consent	X					
Random group allocation			X			
Intervention						
Treat4ALL						
Usual care						
Assessments						
Quantitative survey						
Sociodemographics and alcohol coping skills		X				
Readiness to change alcohol use Social desirability, sexual risk, HIV testing history, PrEP use history, PrEP knowledge and willingness, and ART initiation		X			X	X
HIV-related stigma, depression, health status, quality of life					X	X
Qualitative interviews (Treat4All arm only)						X
Primary outcomes						
Heavy drinking days (TLFB)		X			X	X
Engagement in HIV prevention (PrEP use) or treatment (viral suppression)		X				X
Secondary outcomes						
All participants						
PEth level^*^		X				X
STI prevalence		X				X
People with HIV only						
Viral suppression		X				X
ART adherence		X			X	X
People at risk for HIV only						
PrEP use		X				X
HIV incidence						X

^*^Dried blood spots will be collected from all participants.

The baseline questionnaire is a quantitative assessment that will be performed before arm allocation with participants by trained field staff and completed safely in a confidential place. The survey will be administered to gather information on alcohol use, including self-reported percentage of heavy drinking days measured by the timeline followback (TLFB),readiness to change alcohol use, alcohol coping skills, sociodemographics, social desirability, sexual risk, HIV testing history, PrEP use history, PrEP knowledge and willingness, ART initiation, and self-reported ART adherence. Before the start of the RCT, we will pilot the baseline survey and administration procedures with up to 40 people with similar characteristics to our target population (*n* = 20 PWH; *n* = 20 people at risk for HIV). The pilot will be assessed for survey length and checked for response distribution, item comprehension, and data-collection procedures.

Participants will also complete a series of laboratory assessments at baseline. (1) Urine samples will be collected from all participants with consent and tested for the presence of chlamydia, gonorrhea, or syphilis. (2) Blood samples will be collected from all PWH and sent to the UNC Project Malawi laboratory to assess HIV-1 RNA levels using the Abbott RealTime HIV-1. (3) Finger-stick dried blood spots (DBS) will be collected from all participants for phosphatidylethanol (PEth) testing to detect alcohol use during the 21 days before the study visit (48–50). Samples will be kept in a dry box with a humidity indicator card to monitor the moisture levels until they are brought to the laboratory. Samples will be taken to the local laboratory for storage and shipment processing. PEth is detected in whole blood by an LC–MS/MS assay using dried blood spots (United States Drug Testing Laboratories, Des Plaines, IL, USA). PEth is specific to alcohol metabolism, and slow degradation allows alcohol detection for ~21 days. PEth levels are useful for detecting changes in drinking habits within a participant over time. In 2022, the Society of PEth Research (PEth-NET) produced a 2022 Basel Consensus Document recommending a whole blood PEth cutoff concentration of 20 ng/mL as strongly suggestive of drinking more than minimal amounts (50).

All participants will be asked to complete 3- and 6-month follow-up visits. At months 3 and 6, participants will receive a quantitative follow-up survey that will gather updated information from the baseline on alcohol use, HIV testing history, health status, quality of life, social desirability, readiness to change alcohol use, social support, depression, HIV-related stigma, sexual risk behaviors, PrEP knowledge and willingness, PrEP initiation, and ART initiation and adherence. A laboratory assessment during the month 6 visit will repeat baseline collection, including urine collection for chlamydia, gonorrhea, and syphilis testing; blood sample collection from PWH for HIV-1 RNA testing; and finger-stick DBS collection for Peth testing. Additionally, all participants who tested negative for HIV at baseline will be tested for HIV following the Malawian National HIV Testing and Counseling guidelines, which indicate three serial HIV antibody rapid tests.

We will collect detailed information on alcohol use through the Alcohol Timeline Followback (TLFB) to obtain the number of heavy drinking days, percentage of days abstinent, drinks per drinking day, and measure changes in drinking over time (51). This interviewer-administered assessment reconstructs a daily behavioral calendar to prompt memory recall for alcohol consumption. TLFB has demonstrated good test–retest reliability, convergent validity, and agreement with collateral reports on daily drinking (52, 53). Specific quantities of alcohol consumed will be collected for each day for the 21 days (mirroring the consumption time frame detected by PEth) prior to the baseline, 3, and 6-month assessments. Daily alcohol consumption will be recorded as the number of standard drinks consumed. In general, and as we have previously used in Malawi, 341 mL of beer, 142 mL of wine, 34 mL of liquor/commercial spirit, a 50 mL sachet of local spirit distilled from grains, sweet potatoes, or sugar cane, a 330 mL can of fruit ale, or a 1,000 mL packet of chibuku will equal one standard drink (54–56). An alcohol biomarker will be randomly ascertained in 25% of the participants to validate self-reports at 6 months. The *proportion of heavy drinking days in month 6 will be defined as the proportion of days of heavy drinking (≥4 drinks per day for men and ≥3 drinks per day for women) in the past 21 days*. DBS samples will be collected from all participants. Based on budgetary constraints, a subsample (25%) will be randomly selected for alcohol biomarker testing, equally distributed from the Treat4All or usual care arms. This approach allows for objective measurement of alcohol use while balancing feasibility within a pilot trial context. PEth results >20 ng/mL will be defined as evidence of recent heavy drinking (50, 57, 58). Participants who self-report <50% for heavy drinking days but have PEth results >20 ng/mL will be assigned a proportion of 50% for heavy drinking days within the previous 21 days (50).

Following our theoretical premise that TrEAT will impact HIV prevention and treatment behaviors, we define our co-primary outcome of successful engagement in HIV prevention or treatment with parallel behaviors across HIV status: PrEP use for people at risk of HIV and viral suppression for PWH at 6 months. *PrEP use will be defined as a self-report of >1 pill in the past seven days a month 6. Viral suppression will be defined as an undetectable viral load (<40 copies/mL) at month 6*. Our primary outcome will not be stratified by HIV status. However, we will also assess viral suppression and PrEP use separately among PWH and those at risk for HIV, respectively, as secondary outcomes. In this way, we will assess the short-term efficacy of Treat4All among all participants (inclusive of HIV status) and separately among PWH and those at risk for HIV.

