### Data analysis

3.1

We will first explore the distribution of continuous and categorical baseline variables using descriptive statistics and graphical representations, as appropriate (60). We will then conduct intent-to-treat comparisons between arms, using a log link and binomial error distribution to compare the proportion of heavy drinking days and engagement in HIV prevention or treatment (co-primary outcomes). For the proportion of heavy drinking days, we will estimate the self-reported percentage of heavy drinking days measured by the TLFB at 6 months. We will evaluate the extent to which mean values differ across groups using the deviance χ^2^ (61). As the effect of the intervention may differ by age and sex, effect modification by these factors will be examined. For successful engagement in HIV prevention or treatment, the design effect introduced by participant randomization will be addressed using a robust variance estimate. Probability ratios (PR), analogous to prevalence ratios at a specific time point, with 95% confidence intervals, will be used to estimate and compare the proportion of participants in each arm who achieved the outcome (successful engagement in HIV prevention or treatment) at 6 months. All analyses will also be sex-stratified to explore differences by sex to inform power calculations for a future implementation effectiveness trial. A significance level of 0.05 and two-sided 95% CIs will be used with no adjustment for multiple testing (62).

Additional analyses will assess self-reported ART adherence (among PWH), biologically confirmed HIV incidence (among HIV-negative participants), PrEP use (among HIV-negative participants), viral suppression (among PWH), and biologically confirmed STIs (among all participants). We will also assess the possibility of selective differential attrition across the arms at each post-baseline visit. We will estimate and compare an *a priori* set of baseline demographics by the study arm. If an imbalance is found, we will produce post-baseline regression-adjusted outcome estimates by recalibrating the baseline distribution of that group to the baseline distribution across all groups combined (63).

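### The PEth-triggered substitution of 50% heavy drinking days conflicts with the analysis section, rests on a cut-off that does not support it, and can distort the co-primary effect in either direction

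*Protocol article*

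**What the plan says.** In Effectiveness outcomes and study measures (2.5), the month-6 drinking outcome is the share of the past 21 days that were heavy, from the TLFB. Three further statements in that section bear on it:

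- Testing is partial: "a subsample (25%) will be randomly selected for alcohol biomarker testing, equally distributed from the Treat4All or usual care arms". Its stated purpose is validation: "An alcohol biomarker will be randomly ascertained in 25% of the participants to validate self-reports at 6 months".
- The cut-off is read as heavy drinking: "PEth results >20 ng/mL will be defined as evidence of recent heavy drinking". Earlier in the section its source is described as "recommending a whole blood PEth cutoff concentration of 20 ng/mL as strongly suggestive of drinking more than minimal amounts".
- A positive result changes the outcome: "Participants who self-report <50% for heavy drinking days but have PEth results >20 ng/mL will be assigned a proportion of 50" (per cent).

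Data analysis (3.1) describes the same co-primary outcome without any replacement: "we will estimate the self-reported percentage of heavy drinking days measured by the TLFB at 6 months". The Abstract and Trial design (2.1) present PEth as corroborating the drinking outcome, and Table 1 lists PEth level as a secondary outcome.

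**The concern.** There are three separate faults.

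1. **Two definitions.** Section 2.5 alters some TLFB values and section 3.1 analyses the TLFB percentage as reported. Two analysts could follow the article faithfully and obtain different co-primary results.
2. **An unsupported value.** A sign of more than minimal drinking is turned first into heavy drinking and then into half of all days. Someone who truthfully reports 3 heavy days of 21 (14.3%) is not contradicted by a PEth result above 20 ng/mL.
3. **Two scoring rules in one outcome.** That participant is scored 14.3% if not selected for testing and 50% if selected and positive, with drinking and report identical.

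Power considerations and sample size calculations (3.2) says the pilot is to estimate effect sizes for a fully powered trial, so any distortion would be carried forward.

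**Working it through.** **The plan's own figure.** The article quantifies nothing about the substitution. Its one sizing figure, more than 80% power for 80% vs 96% with 144 participants, reproduces. With 72 per arm and a pooled proportion of 0.88, the null standard error (SE) is √(2×0.88×0.12/72) = 0.0542 and the alternative SE is √((0.16+0.0384)/72) = 0.0525. Then z = (0.16 − 1.96×0.0542)/0.0525 = 1.03, giving 84.8% power. The randomised number is 144/0.9 = 160.

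**Who is affected.** Tested: 0.25×80 = 20 per arm, or 0.25×72 = 18 after 10% loss. Only tested participants who report 0 to 10 heavy days of 21 (at most 47.6%) and are PEth-positive are changed, always upward.

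**The assigned value.** 0.5×21 = 10.5 days, between the reportable 10/21 (47.6%) and 11/21 (52.4%). It is not a count that the binomial error model in section 3.1 describes.

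**Closed form.** Let Δ be the TLFB difference between arms and Δπ the difference in PEth-positive share (usual care minus Treat4All). Suppose every tested value is below 50% and PEth-negative participants have no heavy days. The tested quarter's mean in each arm is then 0.5×(PEth-positive share), and

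ratio of effects = 0.75 + 0.25×(0.5×Δπ)/Δ.

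- Everyone PEth-positive in both arms (Δπ = 0): ratio 0.75, so 16 points become 12.
- Break-even at Δπ = 2Δ: gaps in positivity of 10, 20 and 32 points for TLFB differences of 5, 10 and 16 points. A smaller gap shrinks the effect and a larger gap inflates it.

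**Simulation.** The article gives neither a drinking distribution nor a PEth-positive rate, so these are assumptions. Person-level heavy-day rates are beta-distributed (parameters summing to 3), with 21 binomial days, 25% tested and 1,000,000 persons per arm. PEth-negative participants have no heavy days, all others are PEth-positive, and self-report is accurate. Ratios come from unrounded differences.

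| Drinkers' mean, usual care vs Treat4All | PEth-negative, usual care vs Treat4All | TLFB difference (points) | With substitution | Ratio |
|---|---|---|---|---|
| 50% vs 34% | 0 vs 0 | 16.0 | 13.6 | 0.85 |
| 40% vs 24% | 0 vs 0 | 16.0 | 13.1 | 0.82 |
| 40% vs 24% | 10% vs 20% | 16.8 | 14.9 | 0.89 |
| 40% vs 24% | 10% vs 50% | 24.0 | 24.2 | 1.01 |
| 40% vs 40% | 10% vs 30% | 7.9 | 8.8 | 1.11 |
| 25% vs 20% | 10% vs 40% | 10.5 | 11.9 | 1.14 |
| 30% vs 30% | 10% vs 30% | 6.0 | 7.2 | 1.20 |

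**Size against precision (second row).** The person-level variance is μ(1−μ)/21×(1+20/4), which is 0.0686 at 40% and 0.0521 at 24%. The SE of the difference is √((0.0686+0.0521)/72) = 4.1 points. The shift of 16.0 − 13.1 = 2.9 points is about 0.7 SE, and illustrative power falls from 97% to 90%.

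**If Treat4All participants under-report.** Take no true difference, a 30% mean among drinkers, 10% PEth-negative in both arms, and 40% under-reporting in Treat4All only. TLFB alone then shows a false 10.8 points and the substitution leaves 9.0. It removes 1.8/10.8 = 17% of the error, because the untested 75% alone contribute 0.75×10.8 = 8.1 points.

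**The case against.** The rule has a legitimate purpose. Participants know their arm, counselled participants may under-report, and the Discussion says PEth is there to counteract self-report bias. A correction that only moves values upward is what one would expect for under-reporting. Testing is random and balanced by arm, so with no true or reporting difference the rule creates no expected difference. The section cites three sources for reading the cut-off as heavy drinking and describes only one of them. If section 3.1 governs, the 50% value never enters the primary analysis and no bias follows, and an unseen analysis plan may say so. In a pilot of this size the likely shift is also less than one standard error.

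Much of this stands, and it limits the point. A reader might infer that the rule necessarily biases the effect toward zero. The documents do not support that: they give no drinking distribution or PEth-positive rate, and the direction turns on the between-arm gap in positivity. A reader might also infer that a whole quarter of the outcomes is overwritten. In fact only tested participants who are PEth-positive and report below 50% are changed.

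The defence does not rescue the rule itself. The 50% assignment cites only the source that the article describes as indicating more than minimal drinking. As a correction for under-reporting it reaches at most the tested quarter and removes little of the error. The conflict between sections 2.5 and 3.1 lies in the published text, whatever another document may add.

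**Conclusion.** The point holds as an internal contradiction and an unsupported substitution, not as a bias of known sign. Followed as written, section 2.5 gives a co-primary outcome scored by one rule in untested participants and another in tested ones, with an assigned value that the described cut-off does not justify. Section 3.1 defines the outcome without that rule.

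If the substitution is used and self-report is accurate, the effect was about 0.75 to 1.20 times the TLFB-only effect in the scenarios examined. These are illustrations, not limits. Values below 1 are most plausible when most participants in both arms remain PEth-positive, and values above 1 arise when Treat4All acts mainly by producing PEth-negative participants. With heavier under-reporting in Treat4All, shrinkage is partly corrective but small (10.8 to 9.0 points). If section 3.1 governs, there is no distortion and only the wording conflict remains.

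**What to change.** Reconcile sections 2.5 and 3.1 before unblinding:

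- State that the co-primary outcome is the TLFB proportion of heavy drinking days at month 6 for every participant, and remove the 50% substitution from the primary analysis.
- Use the 25% PEth sample as validation data. Report PEth by arm, and TLFB/PEth discordance separately by arm.
- If a biomarker-corrected estimate is wanted, present it as a sensitivity analysis, for example by imputing from the validation subsample within arm.
- Describe the 20 ng/mL cut-off consistently in both places where it appears.

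This costs wording and one sensitivity analysis, with no new data. The downside is that the co-primary outcome becomes openly self-reported with no biomarker correction, as it already is for the untested 75%. The validation sample is also small: with about 18 tested per arm, a discordance of 50% has a 95% half-width of 1.96×√(0.25/18) = 23 points, so differential under-reporting could be described but not firmly excluded.
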